## Abstract

South Africa developed the differentiated service delivery (DSD) model to improve access to healthcare for people living with HIV (PLHIV), especially key populations (KPs) including female sex workers (FSWs) who often face barriers in accessing HIV services. The DSD model, aims to reduce the burden on healthcare users, healthcare workers, and the healthcare system, can significantly benefit this group. However, the success of the DSD model in achieving the desired HIV treatment outcomes for FSWs has been barely evaluated. This paper describes the protocol for evaluation of the DSD model in improving HIV treatment outcomes among FSWs in Gauteng Province of South Africa. Both qualitative and quantitative methods will be utilized to address three study objectives: stakeholder analysis, mapping, and in-depth interviews (objective 1); programme evaluation of the DSD model in selected sites (objective 2); and development of a framework for optimizing the DSD model in improving HIV treatment outcomes (objective 3). Quantitative statistical analysis will be performed using STATA version 17 (College Station, TX, USA). Qualitative analysis will be performed using ATLAS.ti. This study will provide new insights into the utilization of the DSD model among FSWs in South Africa. It will also inform new strategies for the DSD model’s implementation in the country. This study will contribute towards the development of a framework for strengthening the DSD model in improving HIV treatment outcomes among FSWs in Gauteng Province.

## 1. Introduction

South Africa has a generalized human immunodeficiency virus (HIV) epidemic, with an estimated 8 million people living with HIV (PLHIV) in 2022, and this equates to a total HIV prevalence of 13.2% with more women affected than men [1,2]. The number of new HIV infections was estimated at 164,228 in 2022, reflecting a decline across all age groups and in both females and males since 2016 [1]. The prevalence of HIV among female sex workers (FSWs) in South Africa is projected to be in the range of 39–89% in different locations of the country [3]. Most recently, the Thembisa model estimated the prevalence of HIV among FSWs at 58,8% [1]. Additionally, Kassanjee et al. [3] reported an HIV prevalence of 62% among FSWs. The heightened HIV risk among FSWs is exacerbated by punitive laws that increase vulnerability, pushing them into unsafe environments and intensifying economic hardships, while substance and alcohol abuse, coupled with multiple sexual partners, further compound these risks [4,5]. South Africa is dedicated to achieving the Joint United Nations Programme on HIV/AIDS (UNAIDS) 95-95-95 targets by enhancing HIV prevention, treatment, and care. The country aims to eliminate HIV as a public health issue by 2030 by addressing barriers and promoting fair access to services [4]. South Africa is currently falling short of the second 95 target, which seeks to have PLHIV receive treatment. So far, only 80% of the general population has met this target, with even lower rates among key populations (KPs), according to data from the District Health Information System (DHIS) that is collected by the National Department of Health (NDoH) [1,6].

South Africa has the largest antiretroviral therapy (ART) programme globally, providing treatment to around 5.6 million people living with HIV (PLHIV). Among these, approximately 3.4 million individuals are receiving first-line ART, 145,000 are on second-line ART (SLART), and over 700 are utilizing third-line ART (TLART) [7]. In order to improve HIV treatment and care in PLHIV, the differentiated service delivery (DSD) model, also known as the “patient-centered” strategy, was implemented and has become an integral component of the HIV cascade programmes [8,9]. It consists of four building blocks, namely *When is care provided? Where is care provided? Who provides the care? And what care or services are provided?* [10]. The DSD model is an approach that offers a more adaptable and patient-focused approach to HIV care by customizing services to the diverse needs of different populations [10]. It facilitates the delegation of tasks to community healthcare workers and provides care in more convenient locations, such as community-based settings, rather than limiting it to traditional clinics. Notable features of the DSD model include longer medication refill intervals, reduced frequency of follow-up appointments, support for medication adherence, and the integration of various health services. Additionally, it emphasizes the vital importance of involving the community in providing care [8,11].

Traditionally, South Africa’s HIV care system used a uniform approach where all patients followed the same treatment plans and visited clinics frequently, regardless of their individual needs. This system caused problems, especially for KPs like FSWs and people in remote areas, leading to high drop-out rates, poor treatment adherence, and suboptimal viral suppression [11]. In improving the DSD model, South Africa shifted care to local clinics, giving more responsibility to nurses and community health workers, and offering multi-month prescriptions for stable patients. These strategies alleviated clinic overcrowding and improved patient retention by making healthcare more accessible and personalized [11,12,13]. However, challenges remain, including linking KPs to care, improving rural infrastructure, and integrating HIV treatment with other conditions like tuberculosis and chronic diseases [4].

In settings with limited resources and high demands of PLHIV, the DSD model is being implemented to reduce visits to health facilities for HIV services. For instance, ART refills are frequently separated from clinical visits in the DSD models. Due to COVID-19 restrictions and lockdowns, national HIV policies swiftly adapted, expanding eligibility for decentralized HIV treatment, prolonging ART refills, introducing virtual care models, and enhancing community-based treatment approaches [14]. These approaches included extending ART refills, using telehealth for follow-ups and support, and employing community-based strategies.

The above adaptations have been implemented within the general population due to the absence of disaggregated data on key populations (KPs) in the DHIS. However, a study by Wang et al. [15] showed that the Centralized Chronic Medication Dispensing and Distribution (CCMD) system effectively supported differentiated care for clinically stable PLHIV. The PLHIV participating in the programme maintained high rates of viral suppression and retention, showing that community-based ART delivery did not negatively affect their treatment outcomes [15].

In a separate study, the “Teen Club” programme, which focused on adolescents accessing ART through a youth-centered differentiated care model, reported higher attrition compared to standard care [16]. While most DSD models have been designed for the general population, they often lack specific data on HIV outcomes for KPs, limiting the reporting on how effective these models are in improving treatment for groups FSWs. Additionally, coverage of these models for FSWs remains lower compared to the general population.

This paper aims to describe the protocol for evaluating the DSD model in improving HIV treatment outcomes among FSWs for the decentralization of HIV care in South Africa. By outlining the objectives and methodology in a rigorous, standardized approach, the protocol serves to inform stakeholders, foster collaboration, and establish a baseline for future assessments. This is essential for advancing evidence-based strategies that enhance HIV treatment access and outcomes for FSWs.

### Research Questions

The proposed study will answer the following questions:○What are the experiences, challenges, opportunities, and successes in the implementation of the DSD model by stakeholders in Gauteng Province in South Africa?○Does the DSD model enhance the achievement of HIV treatment outcomes among FSWs in South Africa?○How is the DSD model being utilized among FSWs in Gauteng Province? How are the HIV clinical outcomes of FSWs monitored?

## 2. Methods

The proposed study will follow a mixed-methods approach involving stakeholder analysis, mapping, and in-depth interviews with stakeholders on the DSD model (objective 1); programme evaluation of the DSD model in selected sites in Gauteng Province (objective 2) as well as developing a framework for the optimization of the DSD model in improving HIV treatment services among FSWs (objective 3).

### 2.1. Methods for Objective 1

To identify and solicit the views of stakeholders regarding their interests, successes, challenges, improvements, and experiences in the implementation of the DSD model in South Africa.

This objective will comprise of stakeholder analysis, mapping, and in-depth-interviews with stakeholders.

#### 2.1.1. Methods for Stakeholder Analysis and Mapping

The stakeholder analysis and mapping is a method used to identify which stakeholders to engage, their interests and relevance, as well as inter-relationships [16]. In this regard, a stakeholder analysis and mapping will be conducted to identify and prioritize stakeholders, and assess their interests, successes, challenges, improvements, and experiences in the implementation of the DSD model in South Africa. This method will be carried out in four stages: defining the stakeholders in the context of the DSD model (Stage 1); understanding the stakeholder’s interest/relevance to the DSD model (Stage 2); assessing stakeholder’s influence on the DSD model (Stage 3); and developing strategies for engagement (Stage 4) [17].

Stage 1—Define the stakeholders involved in the implementation of the DSD model: A snowballing method will be used to identify key stakeholders by asking individuals from both governmental and non-governmental organizations (NGOs) to recommend people they consider influential in implementing the DSD model among FSWs in South Africa. Stakeholders will be selected from various sectors involved in the HIV care continuum, including prevention, treatment, care, and support services, as well as those directly linked to the DSD model. Organizations of interest will include government health and social departments, NGOs, community-based organizations (CBOs), implementing partners, civil society organizations (CSOs), United Nations agencies, and multilateral funding bodies.

Stage 2—Understanding stakeholders’ interests with regards to the DSD model: a list of potential stakeholders will be created based on the information gathered in Stage 1.

Stage 3—Assess stakeholders’ influence on the implementation of the DSD model: This step will involve evaluating the stakeholders’ influence on the project and its outcomes. A four-quadrant matrix will be used to map out each stakeholder’s level of interest and influence in the DSD model’s implementation.

Stage 4—Developing strategies for engagement: communication strategies will be developed, which may include creating communication plans, organizing meetings, or establishing incentives to ensure stakeholder engagement [17].

#### 2.1.2. Methods for In-Depth Interviews with Stakeholders

##### Study Design

An exploratory study design will be employed to obtain in-depth information about the subject matter.

##### Study Population

The study population will be drawn from the list of stakeholders identified through the stakeholder analysis and mapping in objective 1. Stakeholders will comprise policymakers, executives, coordinators, supervisors or managers, advisory, informing and advocacy roles, FSWs, and PLHIV involved in different areas (i.e., HIV prevention, treatment, care, and other supportive interventions) of the DSD model.

##### Sample

A purposive sample of 15-20 stakeholders aged 18 years and above will be recruited to gather rich-textured information on the DSD model [18]. The sample size may change depending on when saturation is reached, i.e., when no new information is received from stakeholders. Stakeholders who are willing to voluntarily grant written informed consent and are working in the selected study area will be included to take part in the in-depth interviews. Additionally, consent will be sought for audio recording from the stakeholders.

##### Recruitment of Participants

The implementing partners will link the researcher to the gatekeepers or managers, who will in turn assist with inviting potential stakeholders to participate in this study. Stakeholders will be invited to attend information sessions at implementation sites, where they will receive a study information letter outlining this study’s objectives, participation expectations, and the researcher’s contact details. Alternatively, the information letter may be emailed to potential stakeholders. Since the implementing partners and managers hold access to stakeholders’ personal and contact information, they will be responsible for sharing the study details with them. Stakeholders interested in participating in the in-depth interviews will reach out to the researcher to arrange a convenient time, date, and location for the interview.

##### Data Collection

Face-to-face, in-depth interviews will be carried out with stakeholders using a set of guiding questions. These questions will concentrate on the current DSD model, initiatives, structures, and relevant policies regarding priority areas, needs, gaps, and opportunities. The guiding questions will be tailored to the specific stakeholders and FSWs. Field notes will be recorded during the interviews to supplement the audio data in case of equipment malfunction. The interviews will conclude once data saturation is reached or if the stakeholders choose not to continue.

##### Data Analysis

The data will be captured on ATLAS.ti version 22 (Scientific Software Development GmbH, Berlin) or related software. Inductive coding will be used and generated from ATLAS.ti or related software [19]. Before data analysis is performed, the interviews will be transcribed. Thereafter, the dataset will be read to come up with codes. ATLAS.ti’s inter-coder agreement will be used to deal with discrepancies [19]. Themes and sub-themes will be created using the data (thematic content analysis).

### 2.2. Methods for Objective 2

To conduct programme evaluation of the DSD model in improving HIV treatment outcomes among female sex workers in selected facilities in Gauteng Province.

#### 2.2.1. Study Design

A participatory evaluation approach using both quantitative and qualitative methods will be utilized.

#### 2.2.2. Study Population

The target population will be the Department of Health (DoH) implementing partners that have executed the DSD model for HIV treatment services among FSWs in Gauteng Province. Implementing partners affiliated with the DoH, who have been providing HIV treatment services for at least a year and have a gatekeeper permission in place, will be included. The inclusion criteria for the DSD model implementors, coordinators/managers, internal programme staff, FSWs, and external stakeholders will be those aged 18 years and above, providing HIV treatment services for at least a year or who have utilized HIV treatment services in the last year, knowledgeable on the DSD model for HIV treatment services, as well as willing to take part in the study.

#### 2.2.3. Sample

A purposive sampling procedure will be utilized to select four to six primary implementing sites. Within each implementing sites, 10 DSD model implementors, coordinators/managers, programme staff, FSWs, and external stakeholders will be interviewed. In total, 40 individuals will be interviewed across the four primary implementing partners sites.

#### 2.2.4. Data Collection

Inventory of services will be completed using a questionnaire informed by the Consolidated Framework for Implementation Research (CFIR) 2.0 [20]. The questionnaire will include open-ended questions, to gain insights about the DSD model resources and personnel, and close-ended questions. The qualitative component will be reported following the Consolidated Criteria for Reporting Qualitative Research (COREQ) to ensure thoroughness and precision [21]. For the quantitative component, the reporting will be guided by the Strengthening the Reporting of Observational Studies in Epidemiology (STROBE) checklist [22]. Data will be collected on the DSD model activities and components, including barriers and facilitators, services, implementation, [20] and HIV treatment outcomes (see Table 1).

#### 2.2.5. Data Source

De-identified data will be requested from the provincial DoH implementing partners that have implemented the DSD model for HIV treatment uptake among FSWs in Gauteng Province. The data will include programme data, reports, and other pertinent documents related to the implementation of the DSD model. The focus will be on data collected from January 2019 and onwards. The changes in service, implementation, and HIV treatment outcomes will be compared before and after the implementation of the DSD model.

This evaluation will provide information on whether the DSD model is achieving the desired outcomes and identify opportunities for quality improvement, optimal utilization of resources, and support for staff and managers to improve the programme and make modifications as needed. This will be used to further strengthen programme effectiveness and future development.

#### 2.2.6. Data Analysis

Thematic content analysis will be performed for the data obtained using the open-ended questions. Themes and sub-themes will be formulated in line with the CFIR 2.0 constructs [20]. Analysis will be completed using ATLAS.ti software.

Descriptive analysis will be performed and reported as proportions (n) and frequencies (%) using the latest version of STATA software version 17 (College Station, TX, USA). An interrupted Time series analysis will be completed to assess the changes in service, implementation, and HIV treatment outcomes (Table 1) before (April 2019) and after (January 2020 and onwards) the implementation of the DSD model. The DSD model will serve as the interruption, and comparison will be conducted for two periods (before and after the DSD model).

### 2.3. Methods for Objective 3

To develop a framework for optimization of the DSD model, synthesizing results from objectives 1 and 2.

The development of a framework for optimizing the DSD model in improving HIV treatment outcomes will include the triangulation and synthesis of information from objectives 1–3. This will be guided by the WHO building blocks and analysis of the four building blocks in terms of when, where, who, and what will be [10]. The WHO building block will be used to synthesis the results of objectives 1 to 2 to construct a framework for optimizing the DSD model, building on the evidence provided by the implementation of the WHO building blocks in defining “*When refers to the frequency of service delivery, Where refers to the place of service delivery, Who refers to the person providing the service and What is regarding the services offered*” [10].

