## Figures and Tables

**Table 1 mps-07-00089-t001:** Service, implementation, and HIV treatment outcome measures.

Outcome Category	Indicator
Service outcomes	“*Accessibility; Coverage; Efficiency; Effectiveness; Efficacy; Quality services; Timeliness; and People-centeredness*” [20]
Implementation outcomes	“*Service acceptability (comfort/relative advantages); Appropriateness (utilization rates on innovation, proportion offered, and accepted); The credibility of implementing programs and policies; Uptake and fidelity; Feasibility (utility and practicality); Durability and reach; Service utilization and availability (rates and timing of utilization of services at different time periods); Scalability sustainability (maintenance and routinization)*” [20]
HIV treatment outcomes	Number/percentage of FSWs: reached; tested for HIV linked to HIV care; initiated on HIV treatment; and adhering to HIV treatment and viral load suppression

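### Read literally, the interrupted time series has one pre-implementation month (April 2019), so the pre-DSD trend cannot be estimated and 11 requested months of 2019 fall in neither period

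*Protocol article*

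**What the plan says.** Section 2.2.6 of the protocol article names the method: "An interrupted Time series analysis will be completed to assess the changes in service, implementation, and HIV treatment outcomes (Table 1"). It dates the two sides of the comparison as "before (April 2019) and after (January 2020 and onwards) the implementation of the DSD model", and adds: "The DSD model will serve as the interruption, and comparison will be conducted for two periods (before and after the DSD model"). Section 2.2.5 describes the extract: "The focus will be on data collected from January 2019 and onwards". It also announces the before/after comparison, without a cut-off date: "The changes in service, implementation, and HIV treatment outcomes will be compared before and after the implementation of the DSD model".

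The HIV treatment outcomes in Table 1 are counts or percentages along the cascade: "Number/percentage of FSWs: reached; tested for HIV linked to HIV care; initiated on HIV treatment; and adhering to HIV treatment and viral load suppression".

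The article does not say when DSD began at the sites, why April 2019 was chosen, whether May to December 2019 is a transition period, or what the time unit of the series is.

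**The concern.** An interrupted time series estimates an intervention effect by projecting the pre-intervention trend forward and comparing it with what was observed. The pre-period therefore has to be long enough to show a trend, and its end has to be tied to the date of the interruption. Here the before side is a single calendar month, the after side is an open range, and eight months between them are assigned to neither although only two periods are named. January to March 2019 lies inside the data request but outside the stated before period.

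The time series is the only inferential analysis that the article names, and it describes no comparison group. This analysis is therefore the main quantitative answer to the research question of whether DSD improves HIV treatment outcomes, and it feeds the framework in objective 3. With no estimable pre-trend it reduces to a before/after contrast, which cannot distinguish a change due to DSD from a trend already under way.

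**Working it through.** The plan gives no sample size, power or precision for the time series, so there is no figure to reproduce. The check is whether the model can be fitted and, if so, how precisely.

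**Inputs**
- Pre-period and post-period dates: section 2.2.6.
- Start of the data request, January 2019: section 2.2.5.
- Assumptions, not in the article: monthly points; independent errors with residual SD σ; interruption at January 2020; post-period of 12 months (to December 2020) or 48 months (to December 2023), because the text says only "January 2020 and onwards".

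**Model.** Number the months t, with January 2019 = 1 and January 2020 = 13. Let D = 1 for t ≥ 13. The model is Y = b0 + b1·t + b2·D + b3·D·(t − 13) + error. It has four parameters: b1 is the pre-slope, b2 the level change at January 2020 and b3 the slope change.

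**Step 1: months assigned to neither period, read literally.** January to March 2019 (3) plus May to December 2019 (8) = 11 of the 12 months of 2019.

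**Step 2: rank, read literally.** The only pre-month contributes the row (1, 4, 0, 0). Within the post-months the third column equals the first, and the fourth equals the second minus 13 times the first, so those rows have rank 2. Total rank is 2 + 1 = 3 for four parameters, however long the post-period. The value in April 2019 and the post-period line can be estimated. The pre-slope, level change and slope change cannot be separated.

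**Step 3: precision under other readings.** With n consecutive pre-months of mean m:
- Sxx = n(n² − 1)/12
- SE(pre-slope) = σ/√Sxx
- Pre-line projected to t = 13: variance Vpre = σ²[1/n + (13 − m)²/Sxx]
- SE(level change) = √(Vpre + Vpost), where Vpost, from the same formula for the post-months, is 0.295σ² (12 months) or 0.081σ² (48 months)

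| Pre-period | n | Sxx | SE pre-slope | Vpre | SE level change, 12 post | SE level change, 48 post |
|---|---|---|---|---|---|---|
| January–March 2019 | 3 | 2 | 0.707σ | 60.83σ² | 7.82σ | 7.80σ |
| January–April 2019 | 4 | 5 | 0.447σ | 22.30σ² | 4.75σ | 4.73σ |
| April–December 2019 | 9 | 60 | 0.129σ | 0.528σ² | 0.91σ | 0.78σ |
| January–December 2019 | 12 | 143 | 0.084σ | 0.379σ² | 0.82σ | 0.68σ |

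For January to April: m = 2.5, so Vpre = 1/4 + 10.5²/5 = 0.25 + 22.05 = 22.30. With 48 post-months, √(22.30 + 0.08) = 4.73. The short pre-periods do badly because a steep uncertainty in slope is carried across an eight- or nine-month gap.

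**Step 4: sensitivity to the time unit.** Four weekly points within April 2019 give full rank, but the level-change SE is about 15σ. A finer time unit does not rescue the literal reading.

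**The case against.** The strongest reply is that April 2019 is probably shorthand. A one-point baseline sits badly with a method named as a time series, and if April to December was meant, the model can be fitted with nine points. The level-change SE is then only 0.78/0.68 = 1.15 times that of the full year (48 post-months). This stands: the rank failure belongs to the literal reading. But nothing in the article settles the reading, and the candidates range from not estimable to workable.

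A second reply is that a data request wider than an analysis window is normal, so sections 2.2.5 and 2.2.6 need not conflict. That is fair. The main defect lies inside section 2.2.6, which dates two periods and leaves a gap between them. Nor is this detail that an article leaves to a fuller plan, because the article itself fixes the dates.

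Four stronger inferences are tempting but unsupported.
- A reader might infer that nine pre-months, unlike twelve, prevent season and trend from being separated. With 11 calendar-month terms added (15 parameters), both have rank 14 when there are 12 post-months, and both have full rank with 24 or 48. With 48 post-months the level-change SE is 0.87σ against 0.76σ. The difference is one of precision.
- A reader might infer that every quantitative result of objective 2 is affected. The descriptive analyses in section 2.2.6 need no pre-trend.
- A reader might infer that any existing trend would be credited to DSD whichever reading applies. Where a pre-slope is fitted, the model allows for a linear trend, though very imprecisely with three or four points.
- A reader might infer that all of 2019 is pre-implementation. The article gives no site start date, so that is an assumption.

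**Conclusion.** The point holds for the dates as written. With monthly data, a pre-period of April 2019 alone cannot support the planned segmented regression, and 11 requested months are left in neither period. If the phrase is shorthand, the level-change SE runs from about 4.7σ or more (practically uninformative) down to below 1σ (workable), depending on an interpretation that the text does not fix. It should be fixed before the data are seen, so that the choice cannot follow the results.

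The figures rest on monthly points, independent errors, an interruption at January 2020 and 12 or 48 post-months. Routine programme series are often autocorrelated, so the standard errors serve to compare readings and do not forecast precision. The rank result needs neither the independence assumption nor a particular post-period length.

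**What to change.** In sections 2.2.5 and 2.2.6:
1. State the date on which DSD began, as the interruption, and the time unit of the series.
2. Define the pre-period as every requested month from January 2019 to the month before that date. If DSD began in January 2020, this is January to December 2019, 12 points.
3. State the status of May to December 2019. If it was a roll-out phase, declare it and code it as a separate segment. In that case only, extend the data request to before 2019 where data exist, because four clean pre-months cannot support the counterfactual.

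The cost is a sentence or so in each section. The 2019 months are already within the request. The roll-out case would need a slightly larger extract. Availability of earlier data is unknown, but the Ethics section describes the data-sharing agreement as still to be secured, so the wider window could be raised there.

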## 4. Discussion

There are no evaluations of the DSD model for HIV treatment among FSWs in South Africa, especially during the COVID-19 pandemic. Female sex workers continue to experience barriers in accessing HIV services in the public health domain due to structural (stigma and discrimination) and legal factors [4,5]. South Africa under-performed in terms of having 95% of the PLHIV initiated on ART and this was particularly lower for KPs, including FSWs [1,6]. Additionally, at the height of COVID-19, the DSD model was expanded to improve the delivery and utilization of HIV treatment services among HIV patients outside of health facilities, expanding who was eligible for DSD for HIV treatment. Even though there was an expansion of the DSD model during COVID-19, little is known about how the DSD model improved HIV treatment outcomes of FSWs. Furthermore, little is known about how the DSD model is being implemented for FSWs, what successes and challenges are being experienced, as well as the improvements needed. A female sex workers programme implementing the DSD model has not been evaluated using the scientific approach. This approach will enable the researchers to harness experiences of the FSWs, providers, and implementors with the DSD model of care and HIV treatment cascade, which have not been studied. This study will attempt to close gaps that might have contributed to the implementation of the DSD model among FSWs in South Africa. A context-specific framework that can guide HIV services for FSWs will be critical ahead of the 2030 agenda to end HIV as an epidemic.

This study is aligned to the UNAIDS global strategy (2021–2026) for ending inequalities and AIDS as well as the National Strategic Plan (NSP) 2023–2028, Strategic Goal 1 (“Break down barriers to achieving outcomes for HIV, TB and STIs”) [4]. The NSP’s 2023–2028 Strategic Goal 1 looks at removing barriers to service availability, access, and updates in communities through human rights-based, and people and community-centered approaches [4]. Hence, this study aims to evaluate the DSD model in improving HIV treatment outcomes among FSWs for the decentralization of HIV care in South Africa.

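### The single-interruption, two-period time series cannot separate DSD from COVID-19, so the January 2020 contrast should not be read as a causal DSD effect

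*Protocol article*

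**What the plan says.** Section 2.2.6 (Data Analysis) plans an interrupted time series on the service, implementation and HIV treatment outcomes of Table 1, "before (April 2019) and after (January 2020 and onwards) the implementation of the DSD model". It then fixes the structure: "The DSD model will serve as the interruption, and comparison will be conducted for two periods (before and after the DSD model".

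Section 2.2.5 (Data Source) sets the data window, "The focus will be on data collected from January 2019 and onwards", and the source: "De-identified data will be requested from the provincial DoH implementing partners that have implemented the DSD model". No partner or population without DSD is named as a comparison. The same section states the use of the result: "This evaluation will provide information on whether the DSD model is achieving the desired outcomes". Research question 2 asks whether DSD enhances HIV treatment outcomes among female sex workers.

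On the pandemic, the Introduction says: "Due to COVID-19 restrictions and lockdowns, national HIV policies swiftly adapted, expanding eligibility for decentralized HIV treatment, prolonging ART refills". The Discussion adds that "at the height of COVID-19, the DSD model was expanded to improve the delivery and utilization of HIV treatment services". Section 2.2.6 does not mention COVID-19.

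**The concern.** An interrupted time series without a control series assumes that nothing else moved the outcome at about the time of the interruption. The article's own Introduction and Discussion say that something did: the pandemic changed eligibility, refill intervals and modes of care, and it changed DSD itself. With one interruption and two periods, any net movement after January 2020 enters the DSD level and slope terms, whether it came from DSD, from restrictions, from recovery or from the policy response.

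This is the only inferential analysis the article describes, and its results feed the objective 3 framework. A pattern produced by restrictions and their lifting could be taken as evidence on how DSD works for female sex workers.

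**Working it through.** The article states no effect size, power or expected series for this analysis, so there is no figure to reproduce. The check has three parts: timing, an illustration of bias, and the precision cost of adding terms.

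**1. Timing.** The documents give no date for restrictions. If onset is assumed 0 to 5 months after January 2020 and the series ends in December 2021, 2022 or 2023 (24, 36 or 48 after-months), the share of after-months at or beyond onset runs from 19/24 = 79% to 100%. None of the 2019 months is affected. At most 5 months show DSD without COVID-19.

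**2. Bias when DSD does nothing (illustration).** The monthly model is y = b0 + b1·t + b2·post + b3·(months since January 2020)·post.

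Assumptions, none from the documents:
- true DSD effect 0 and a flat series otherwise;
- a dip of 10 percentage points from month s = 2, 3 or 4 (January 2020 = month 0), lasting 6 months;
- linear recovery over 12 months, its first month still at full depth;
- 9 or 12 pre-months (April or January to December 2019) and 24, 36 or 48 post-months. The pre-period is an interpretation, because the article writes only April 2019.

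The pre-period contains no shock, so the false level change is the intercept, and the false slope change the slope, of a least-squares line through the post-period shock. The pre-period length drops out. Worked case, s = 2 with 24 post-months:
- Sum of shock: 6 × (-10) + (-10) × 6.5 = -125. Mean: -125/24 = -5.21.
- Sum of month × shock: -270 - 758.3 = -1028.3. Centred: -1028.3 + 11.5 × 125 = 409.2.
- Sum of squares of month: 24 × (24² - 1)/12 = 1150.
- Slope: 409.2/1150 = +0.356 points per month.
- Level: -5.21 - 0.356 × 11.5 = -9.30 points.

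Over the whole grid the false level change is -6.80 to -9.30 points and the false slope change +0.138 to +0.356 points per month. Starting the recovery one month sooner gives -6.4 to -9.1 points. Bias is proportional to the dip: a 5-point dip halves it.

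Varying the shape more widely (onset 0 to 5 months, full depth for 3, 6 or 12 months, recovery over 6 or 12 months with mid-month values) gives a level bias of -3.7 to -12.2 points and a slope bias of -0.24 to +0.57 points per month. The slope bias is mostly positive but can reverse: onset at month 5, 12 months at full depth, 12 months' recovery and a series ending December 2021 give -0.24.

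**3. Cost of adding terms.** Standard errors come from σ²(X′X)⁻¹ with independent errors and the same σ, on the part 2 grid.

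| Added to the model | Level-change SE | Slope-change SE | Bias left in DSD level |
|---|---|---|---|
| One 18-month COVID-19 pulse | +5% to +22% | almost unchanged | -1.5 to -3.8 points |
| COVID-19 level and slope from month s | +34% to +73% | × 3.5 to × 16.8 | 0 |

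The pulse also leaves a slope bias of +0.05 to +0.26 points per month. The slope multiplier is large because, once level and slope terms start at month s, only the s earlier months identify the DSD slope. The sum of squares of month is 0.5 for s = 2 and 5 for s = 4. The extremes are:
- s = 2, 12 pre, 48 post: √[(1/0.5 + 1/143)/(1/9212 + 1/143)] = 16.8
- s = 4, 9 pre, 24 post: √[(1/5 + 1/60)/(1/1150 + 1/60)] = 3.5

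**The case against.** The strongest reply is that a condensed article need not list covariates or sensitivity analyses, and that a contrast between two periods does not rule out adjustment. Part of this stands: the absence of a COVID-19 term alone would not be a finding. But the article goes further than silence. It fixes one interruption, two periods and a January 2020 start, so a third period would depart from what is stated.

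Four stronger readings are tempting and are not supported:
- **That COVID-19 change will be reported as the DSD effect.** Section 2.2.6 speaks only of assessing changes, and Section 2.2.5 of information on whether desired outcomes are being achieved. The text supports only that the result could be read that way.
- **That a lockdown drop will look like harm and a rebound like benefit.** The documents never say that an outcome among female sex workers fell. The Introduction describes widened access, so even the direction is open.
- **That research question 2 cannot be addressed at all.** Objective 2 is a participatory mixed-methods evaluation with other evidence. What fails is causal attribution from this contrast.
- **That staggered site start dates would separate DSD from calendar time.** Nothing says that sites started in different months; one date is given.

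It can also be objected that COVID-19 terms absorb part of the intervention, since DSD was itself expanded during the pandemic. That stands, and it limits what any added term can achieve.

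**Conclusion.** The concern holds as a limit on attribution. As written, COVID-era change lies in the after period with nothing to distinguish it from DSD, and the article's own account contradicts the assumption that a single-series design needs. The contrast can describe change across January 2020; it cannot by itself show that DSD caused that change.

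The size is not known. A false level change of about -7 to -9 points rests wholly on an assumed 10-point dip with an assumed date and shape. It shows that the bias can be a large fraction of the shock, not what it will be. The conclusion on timing needs only that restrictions began in the first half of 2020.

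A separate matter should be settled at the same time. April 2019 as the before period does not match data from January 2019 onwards. Read as a single month, it leaves the four-parameter segmented model inestimable (rank 3 of 4).

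**What to change.** In Section 2.2.6:

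1. Replace the two periods with three: before DSD, DSD before COVID-19 restrictions, and DSD from the restrictions onward. Include COVID-19 level and recovery terms at dates fixed in advance.
2. Repeat the analysis excluding the restriction months.
3. State that the January 2020 contrast will be reported as change over the joint DSD/COVID-19 era, not as the causal effect of DSD, unless the adjusted analyses support more.

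The third change is essential and costs only wording. The first two use data already requested, but the precision cost is real. In the illustration, level and slope terms add 34% to 73% to the standard error of the DSD level change and multiply that of the DSD slope change 3.5 to 16.8 times. A single pulse term is cheaper (5% to 22% on the level) but leaves bias behind. Because DSD was itself expanded during the pandemic, even the fuller model may not separate the two, and the plan should say so.
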